## Abstract

**Background:**

Globally, the rapid development of mobile technology has created new ways of addressing public health challenges and shifted the paradigm of health care access and delivery. The primary aim of this study is to examine the effectiveness of Mobile-health on maternal health care service utilization in Eastern Ethiopia.

**Methods/design:**

Through, a cluster-randomized controlled trial, 640 participants will be selected based on their districts and respective health centers as the unit of randomization. All pregnant mothers who fulfill the inclusion criteria will be allocated to a mobile-phone-based intervention and existing standard of care or control with a 1:1 allocation ratio. The intervention consists of a series of 24 voice messages which will be sent every 2 weeks from the date of enrollment until the close-out time. The control group will receive existing standard of care without voice messages. Data related to outcome variables will be assessed at three phases of the data collection periods. The primary outcome measures will be the proportion of antenatal care visits and institutional delivery, whereas the secondary outcome measures will consist of the proportion of postnatal care visits and pregnancy outcomes. Risk ratios will be used to a measure the effect of intervention on the outcomes which will be estimated with 95% confidence interval and all the analyses will be done with consideration of clustering effect.

**Discussions:**

This study should generate evidence on the effectiveness of mobile-phone-based voice messages for the early initiation of maternal health care service use and its uptake. It has been carefully designed with the assumption of obtaining higher levels of maternal health care service use among the treatment group as compared to the control.

**Trial registration:**

Pan African Clinical Trial Registry, www.panctr.org, ID: PACTR201704002216259. Registered on 28 April 2017.

**Electronic supplementary material:**

The online version of this article (10.1186/s13063-018-2446-5) contains supplementary material, which is available to authorized users.

## Background

Mobile phones, which have reached the hands of 90% of the world’s population, of whom 80% are rural dwellers [1], has also made possible Mobile-health/m-health, the usage of mobile technology to improve health. Globally, the rapid development of mobile technology has generated new ways to address public health challenges and shifted the paradigm of health care access and delivery [1, 2]. In the health care system of developing countries, mobile-phone technology is used to report health information and health care is delivered through telemedicine, to populations otherwise deprived, to improve adherence to treatment and appointments [3]. m-health also plays a major role in sexual and reproductive health care and is seen as a key area in achieving the global strategy for women’s and children’s health [4]. Evidence has shown that m-health minimizes time barriers and facilitates urgent care during emergency obstetric referrals and maternal health care use in low- and middle-income countries (LMICs) [5].

Developing regions accounted for approximately 99% of global maternal deaths in 2015, of which sub-Saharan Africa (SSA) alone accounted for about two thirds, followed by one third in Southern Asia. Achieving the Sustainable Development Goals (SDG) target of a maternal mortality rate (MMR) below 70 per 100,000 live births will require a 7.5% reduction of MMR every year between 2016 and 2030 [6]. This will need more than three times the annual rate of global maternal mortality reduction that was observed between 1990 and 2015 [7]. Furthermore, three million babies die every year before they are a month old, and a similar number are stillborn [8, 9]. Most of the deaths are due to lack of quality maternal and neonatal health care service provision [10].

At the moment, many countries, including Ethiopia, are working to meet the recommendation of having skilled birth attendants for all births [11]. However, the maternal health problem is still very serious; every year about 350,000 maternal deaths occur because of pregnancy and its related complications. The problem is more serious in developing countries [11, 12]. In Ethiopia, the mortality rate increased from 673 per 100,000 live births in 2005 to 676 per 100,000 live births in 2011 [13].

Since 2003, Ethiopia has had increasing access to primary health care services through the Community Based Health Extension Program (CBHEP). Between 2003 and 2010, about 34,000 health extension workers (HEWs) were trained and deployed in 15,000 kebeles (villages), each of which had one newly constructed health post (HP) and about 3000–5000 dwellers [12]. Regardless of all these efforts, according to the Ethiopian Demographics Health Survey (EDHS) 2011, the number of women who received antenatal care (ANC) (34%), institutional delivery (10%) and postnatal care (PNC) (6%) services by skilled workers was very small, and this has resulted in high maternal and neonatal morbidity and mortality [11]. To tackle this problem more effectively, practicing innovative ways of health care service delivery, which will be integrated with the existing health care system is crucial, and thus mobile technology is being used. Despite the widespread use of mobile technologies in the health care system, there is limited evidence on the efficacy of mobile-phone-based interventions, or m-health, on maternal health care service utilization. In Ethiopia, no study has been conducted on the topic. To fill the gap, this study, through a randomized controlled trial (RCT), examines the effects of m-health on maternal health care service use in Eastern Ethiopia. It is hypothesized that m-health will increase maternal health care service provision in limited-resource and -literacy settings. In this RCT, two districts that are 34 km apart will be selected to reduce the possible risk of contamination between the intervention and control arms and to evaluate the barriers of implementation. The outcomes of this investigation will be analyzed for both intervention and control arms separately. Examining challenges and outcomes at this stage will provide insight into m-health implementation for improved maternal health care service use.

## Methods/design

### Study design

A single-blind, cluster-RCT study design will be employed on districts and their respective health centers (HCs). Study participants will be randomized to a mobile-phone-based intervention (voice message for reminding and informing about the advantages of maternal health care service use) or existing standard of care (SOC)/control (without voice message) under their respective districts and HCs with a 1:1 allocation ratio (Fig. 1).

**Fig. 1 Fig1:**
[figure not shown]
Consolidated Standards of Reporting Trials (CONSORT) Diagram of study design. This figure depicts sampling method and allocation of study units, assessment of eligibility criteria to include study participants

**Fig. 2 Fig2:**
[figure not shown]
Standard Protocol Items: Recommendations for Interventional Trials (Additional file 1: SPIRIT) Figure for the schedule of enrollment, interventions and assessments. This figure shows the schedule of enrollment, interventions and assessments of the m-health trial study, Eastern Ethiopia, August 2017 to October 2018

**Fig. 3 Fig3:**
[figure not shown]
Summary of conceptual framework. This figure shows that the effects of mobile-phone-based voice message on maternal health care service use

### Study setting

This study will be done in Haramaya and Kombolcha districts, which are in Eastern Haaraghe Zone, Oromia Regional State, Eastern Ethiopia.

Haramaya district, which is about 506 km from Addis Ababa, the capital city of Ethiopia, is located between 9°24′N and 42°01′E and is 1400–2340 m above sea level. According to the 2007 national census of the country, its population was 271,018, of whom 48.97% were women and 18.46% were urban dwellers. Moreover, by using pregnancy rate estimation factors of 4.6%, around 12,467 women are expected to be pregnant in this district. In the district, there are seven HCs, 22 HPs and one hospital, [14].

On the other hand, the district of Kombolcha is 540 km from Addis Ababa and is found at between 1200 and 2460 m above sea level. According to the 2007 national census report, its population was about 140,080, of whom 49.3% were women and 9.01% were urban dwellers. Moreover, by using pregnancy estimation factors of 4.6%, about 6444 women are expected to be pregnant in this district. In Kombolcha, there are five HCs and 22 HPs.

Related to study parameters, like socio-demographics, economic characteristics and maternal health care service coverage, the two districts have similarities [15].

### Participants: inclusion and exclusion criteria

The participants will be recruited from two districts (Haramaya and Kombolcha districts) based on pre-set eligibility criteria (pregnancy, gestational age (GA), ownership of a mobile phone and willingness to participate). The participant will be included in the trial if her GA is less than 16 weeks, she owns a mobile phone and has willingness to participate. The potential trial participants will be identified by the field worker-based enrollment criteria. For all eligible participants, the field workers will explain about study by reading the participant information sheets; if the study subjects are willing to participate, written informed voluntary consent will be obtained and baseline data collection will be made.

In this trial, study women who fulfill the enrollment criteria for the study but are critically ill at time of enrollment will be excluded from the study. Critically ill women are those pregnant mothers who unable to respond to interview questions because of illness. In addition, women with any systemic illness during this time will be excluded from the study. Any pregnant women with systemic illness need an special ANC follow- up, which is different from the recommended routine ANC follow -up and this set precondition without effect of treament for good adherence to maternal health care service use. Hence, any pregnant mother with known systemic illnesswill be excluded from this study.

### Sample size determination

A study which was conducted in Zanzibar showed that 60% of the intervention group used a health-professional-assisted delivery (institutional delivery), as compared to 47% in the control group; based on this evidence, sample size required for this study is calculated as follows [16]:P_1_ = proportion of health professional assisted delivery in control group = 47%P_2_ = proportion of health professional assisted delivery in intervention group = 60%

Based on the above information, a sample size required for this study is calculated by using STATA/SE software with consideration of sample size for a two-sample comparison of proportions [17].

### Assumption and hypothesis for sample size calculation

*H*_o_: *P*_1_ = *P*_2_, whereas *P*_1_ is the proportion in the intervention group (population _1_) and *P*_2_ is the proportion in the control group (population _2_), *α* is level of significance at 95% confidence interval, and *β* is power.

In a cluster-RCT the study subjects within the cluster are more likely to interact, respond in the same manner and can no longer act independently which can lead to a loss of statistical power. This intracluster dependence can be quantified by considering intracluster correction coefficient (ICC) and design effects (DE) [18]. Hence, the estimated sample size per group is inflated by considering ICC, and DE of 1.3. Thus, the final sample size required for this study will be 320 for each control and treatment groups.

*Description of sample size calculation*: a sample size of 640 pregnant mothers (320 in each of the treatment and control group) will be sufficient to detect a clinically important difference of 13% between groups in the m-health intervention, using a two-sided test of 80% power (*β*) and 5% of significance level (*α*) with 95% confidence interval**.** The 13% difference represents the difference between a 60% health-professional-assisted delivery rate in the intervention group as compared to the control group [16].

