### Randomization and sampling procedure

Among the 15 districts in Eastern Hararghe Zone, Haramaya and Kombolcha are selected purposefully because they have better access to electric power and network, which are mandatory for mobile-phone charging and communication during the study period. In addition, the community in these districts has similar socioeconomic and demographic characteristics and maternal health care service coverage [19, 20]. Then, by a lottery method, the two districts are determined as an intervention (m-health + SOC) or a control group (SOC only). Accordingly, Haramaya district is an intervention group (m-health + SOC) whereas Kombolcha is a control (SOC).

Based on the EHSTP of 2016–2020, one HC, which encompasses five HPs in five Kebeles which consisting of 3000–5000 people each, can provide service for 15,000–25,000 people [21]**.** In Ethiopia, the estimated number of pregnancies in a given population is about 4.6% [22]. Hence, the total number of estimated pregnant mothers in five kebeles surrounding one HC is about 690–1150.

Among the seven HCs in Haramaya district, Addelle HC is selected by the purposive method as secondary study unit. The main reason for the purposive selection is accessibility of electric power and network, which will be mandatory for mobile-phone charging and communication during the study period. Finally, all pregnant mothers who fulfill the enrollment criteria in the selected Kebele will be registered and 320 pregnant mothers will be selected for the intervention group by a simple random-sampling method. Likewise, of the five HCs in Kombolcha district, Kombolcha HC is selected purposefully for the same reason, and from the surrounding kebeles, 320 mothers will be selected for the control group by simple random sampling (SRS) method.

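### The design effect of 1.3 does not fit one 320-woman cluster per arm, so the 80% power claim is not established for this design

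*Protocol article*

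**What the plan says.** Under Sample size determination, the protocol article takes its planning rates from an earlier trial in which "60% of the intervention group used a health-professional-assisted delivery (institutional delivery), as compared to 47% in the control group". The next section, Assumption and hypothesis for sample size calculation, explains that women within a cluster do not respond independently and that this costs power. It continues: "Hence, the estimated sample size per group is inflated by considering ICC, and DE of 1.3". The result is that "the final sample size required for this study will be 320 for each control and treatment groups". The 640 women, it says, "will be sufficient to detect a clinically important difference of 13% between groups in the m-health intervention", "using a two-sided test of 80% power" "and 5% of significance level". That section gives no cluster size and no number of clusters.

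Both follow from Randomization and sampling procedure. Two districts were chosen purposively and a lottery made one the intervention arm and the other the control arm. One health centre was then chosen purposively in each district, and 320 women are to be drawn from the area around it. Statistical method plans generalized estimating equations (GEE) to adjust for clustering by district and health centre.

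**The concern.** A design effect is not a free-standing multiplier. It is fixed by the cluster size and the ICC. When a whole arm of 320 women is one cluster, even a very small ICC produces a large design effect, so 1.3 is a strong assumption here. The more basic difficulty is that two clusters in two arms leave nothing from which to estimate how far districts differ without any intervention.

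The power statement is the only justification given for 640 women, and two misreadings are at stake. A null result could be taken as evidence of no effect. Equally, an ordinary difference between two districts could be taken as an effect of the voice messages, because a test that allows for too little clustering rejects too often.

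**Working it through.** **Inputs.** Rates of 47% and 60%, difference 0.13, mean 0.535 (Sample size determination). Two-sided 5% level, 80% power, design effect 1.3, 320 per arm (Assumption and hypothesis for sample size calculation). Equal allocation (Study design). One district and one health centre per arm (Randomization and sampling procedure). No ICC value is given, so every ICC below other than the implied one is an assumption.

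**1. Reproduce the 320.**
- n = [1.96·√(2·0.535·0.465) + 0.8416·√(0.47·0.53 + 0.60·0.40)]² / 0.13² = (1.3825 + 0.5886)² / 0.0169 = 229.9
- With continuity correction: (229.9/4)·[1 + √(1 + 4/(229.9·0.13))]² = 245.04, rounded up to 246
- 246 × 1.3 = 319.8, rounded up to 320

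The plan's figure is reproduced. Without the correction, 230 × 1.3 = 299, which does not match.

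**2. ICC implied by 1.3.** With DE = 1 + (m − 1)·ICC and m = 320:
- ICC = 0.3/319 = 0.00094
- Between-district SD = √(0.00094 × 0.535 × 0.465) = 0.0153, about 1.5 percentage points

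**3. Degrees of freedom.** Two clusters minus two arm means leaves 0 for between-cluster variance. District and treatment coincide exactly, so GEE has no replication from which to separate them. More women do not change this.

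**4. Illustration, with the between-cluster variance treated as known.** Effective n per arm = 320/DE. Continuity-corrected power = Φ{[(0.13 − 1/n_eff)·√n_eff − 1.3825] / √(0.47·0.53 + 0.60·0.40)}. The uncorrected version omits 1/n_eff.

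| Assumed ICC | DE | Effective n per arm | Power, corrected (uncorrected) |
|---|---|---|---|
| 0.001 | 1.32 | 243 | 80% (82%) |
| 0.005 | 2.6 | 123 | 48% (53%) |
| 0.01 | 4.2 | 76 | 30% (36%) |
| 0.02 | 7.4 | 43 | 17% (23%) |

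These figures are optimistic, because the variance taken as known cannot be estimated in this trial.

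**5. Limit of adding women.** With one cluster per arm, effective n = n/[1 + (n − 1)·ICC], which cannot exceed 1/ICC. Even with the variance known, 80% power needs an effective n of 246 (230 uncorrected). Above an ICC of about 0.004 (1/246 = 0.0041; 1/230 = 0.0043), no enrolment in these two districts reaches it.

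**6. False positives.** If the test assumes DE 1.3 and the ICC is 0.01 (DE 4.19), the two-sided type I error is 2·Φ(−1.96·√(1.3/4.19)) = 0.27.

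**The case against.** Several points can fairly be made for the plan.

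- *The arithmetic is correct.* This stands. A reader might infer that 320 was miscalculated, but it follows exactly from the stated inputs. The fault lies in the fit between the design effect and the allocation.
- *The ICC may be in the full protocol.* This also stands: the article says an ICC was considered, and leaving its value to a fuller document is not an error. But the article does fix the design effect, the cluster and the number of women in it, and together these allow only one ICC. Nor would a cited ICC restore the missing degrees of freedom.
- *Power may really be 80%.* A reader might infer that true power is 30% or lower. The documents do not support that, because every figure below 80% rests on an assumed ICC. At 0.00094 or below, the nominal formula gives at least 80% with the correction (83% at 0.00094 without it). What can be said is that the claim is not established.
- *The kebele could be the cluster.* The article describes "one HC, which encompasses five HPs in five Kebeles", which might suggest five clusters of 64 women per arm and an implied ICC of 0.3/63 = 0.0048. That is a general service-planning norm. The number of kebeles sampled in this trial is not given, and kebeles are not what the lottery assigned. The reading neither rescues the calculation nor provides a sound basis for a restated power.

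**Conclusion.** The point holds as a mismatch between the sample size assumption and the allocation. A design effect of 1.3 with one 320-woman cluster per arm requires an ICC of about 0.00094. Whatever the ICC, one cluster per arm leaves between-district variance inestimable and treatment confounded with district. Neither the inflation by 1.3 nor the planned GEE secures 80% power or the 5% error rate for the cluster comparison.

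The loss of degrees of freedom follows from the documents alone. The size of the power loss and the 27% type I error depend on ICCs assumed for illustration. A false positive is as much a risk as a misread null result.

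**What to change.** In Assumption and hypothesis for sample size calculation:

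1. Name the cluster (district with its health centre), its size (320), the number per arm (one) and the ICC that 1.3 implies (about 0.00094).
2. Withdraw the 80% power claim for the cluster comparison, or state that it holds only if the between-district ICC is about 0.001 or less and is treated as known.
3. State that power for a district-level comparison cannot be established with one cluster per arm.

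The cost is one rewritten paragraph and a less favourable power statement, with no added enrolment. Enrolling more women in the same two districts would not answer the point. Randomising kebeles is not proposed: it would be a redesign, at odds with the district lottery and with the 34 km separation that the Background gives as protection against contamination.

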#### Control arm B

Participants in the control group will receive existing SOC which informs them about the advantages of maternal health care service use at HCs, informing them about the service which is given free of charge and giving appointments for regular follow-up. Unlike the intervention group, however, these participants will not be sent the voice message to remind for appointment and information about the advantage of maternal service use. With regards to the data collections, a house-to-house survey will be made among the households which will be identified with pregnant mothers who fulfill the inclusion and enrollment criteria. The three phases of the survey (I, II and III) will be made to collect data from the mothers who are in the trial. The survey will focus on maternal socio-demographic status, maternal health conditions, nutritional status, and health care service use and pregnancy outcome. The data collection tools will be the same for both trial arms (Trial arms A and B), except for mobile-phone-based voice message status.

For either intervention or control group if the study participants move from the study area before the study is completed, or withdraw from the study before the final data collection period, they will be registered as dropouts to follow-up.

Assuming that all mothers may give birth at different GAs their status of delivery will be tracked by fieldworkers and health professionals at selected HCs (Fig. 2).

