### Analysis plan: analysis of primary and secondary outcome

In this study, data will be collected at three phases. Phase I data collection will be done during enrollment time; phase II data collection will be conducted after 4 months of enrollment or after the eighth voice message; and end-line data collection or close-out time data collection (phase III data collection time) will be made after the 24th voice message. All the data will be checked for completeness at the time of data collection, coded and entered into Epi-Info-7 by using double-data entry method and they will be transported to STATA software Version 11 for analysis. Data cleaning will be done by the running of simple frequency distributions for internal consistency.

The report of this findings will be made according to the Consolidated Standards of Reporting Trials (CONSORT) standards for reporting RCTs. This is a behavioral intervention which is unlikely to cause adverse effects. Hence, the analysis will be done after the close-out time of the data collection. Intention-to-treat (ITT) principles will be used for primary outcome analysis; therefore, all the participants will be analyzed according to the arms they will be randomized to. During ITT analysis, the participants lost to follow-up, resulting in missing to maternal health care service use at close-out time of data collection, will be considered as non-health care service users.

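### The 320 women per arm contain no allowance for loss to follow-up, and counting women with missing outcomes as non-users takes power below the stated 80% once more than minimal loss of the delivery outcome occurs

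*Protocol article*

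**What the plan says.** Sample size determination takes its two rates from an outside trial: "proportion of health professional assisted delivery in control group = 47" and "proportion of health professional assisted delivery in intervention group = 60" (both in percent). Assumption and hypothesis for sample size calculation inflates the per-group number for clustering only, with a design effect of 1.3, and concludes "Thus, the final sample size required for this study will be 320 for each control and treatment groups". It adds that 640 women "will be sufficient to detect a clinically important difference of 13% between groups in the m-health intervention", "using a two-sided test of 80% power" and "5% of significance level". Randomization and sampling procedure, and Screening and enrollment procedure, then select exactly 320 per arm, with none added for loss.

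Two other places deal with loss. Under Control arm B, a sentence that covers both arms says that if women move away or withdraw before the final data collection, "they will be registered as dropouts to follow-up". Analysis plan: analysis of primary and secondary outcome says that, in the primary intention-to-treat analysis, women lost to follow-up whose service use is missing at close-out "will be considered as non-health care service users". No expected loss rate is given anywhere.

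**The concern.** The power statement and the missing-data rule do not fit together. The power is stated for a 13-point difference in 320 women per arm, all with a known outcome. The analysis will keep all 320 in the denominator but score women with missing outcomes as failures, so both rates and their difference shrink with every such loss. Loss is plausible: women enter before 16 weeks of gestation and are followed to 45 days after delivery.

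Institutional delivery is one of two primary outcomes and the only one on which the sample size is based. If its power is overstated, a null result will be read as stronger evidence against the intervention than it is.

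**Working it through.** **Inputs from the protocol.** p₁ = 0.47, p₂ = 0.60, two-sided α = 0.05, power 0.80, 1:1 allocation, design effect 1.3, 320 per arm. **Assumed:** loss L, equal in both arms and unrelated to where the woman delivers.

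**1. Reproducing 320.** With p̄ = 0.535 and d = 0.13:

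n = [1.960·√(2·p̄(1−p̄)) + 0.842·√(p₁(1−p₁) + p₂(1−p₂))]² / d²
= [1.960·√0.49755 + 0.842·√0.4891]² / 0.0169 ≈ 229.9, so 230.

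Continuity correction: n_c = (n/4)·[1 + √(1 + 4/(n·d))]² ≈ 245.0, so 246.

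- With the correction: 246 × 1.3 = 319.8, so 320. This matches the protocol.
- Without it: 230 × 1.3 = 299. No match.

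The match is reached with zero loss.

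**2. Effect of the missing-as-non-user rule.** The analysed rates are 0.47(1−L) and 0.60(1−L), and the difference is 0.13(1−L). The denominator stays at 320, so the effective size is 320/1.3 = 246.2 per arm.

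Power = Φ{[d·√m − 1.960·√(2·p̄(1−p̄))] / √(p₁(1−p₁) + p₂(1−p₂))}, using the shrunken rates. Here m = 246.2 without the correction and m = (246.2 − 1/d)²/246.2 with it.

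Example at L = 10%: the rates are 42.3% and 54.0%, and d = 0.117. With the correction, m = (246.2 − 8.55)²/246.2 ≈ 229.4. The numerator is 0.117·√229.4 − 1.960·√0.49932 ≈ 1.772 − 1.385 = 0.387. The denominator is √0.49247 ≈ 0.702. So z ≈ 0.551 and power ≈ 70.9%.

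| Assumed loss, each arm | Difference analysed (points) | Power, with correction | Power, without |
|---|---|---|---|
| 0% | 13.00 | 80.2% | 82.6% |
| 1% | 12.87 | 79.3% | 81.8% |
| 3% | 12.61 | 77.5% | 80.1% |
| 5% | 12.35 | 75.7% | 78.4% |
| 10% | 11.70 | 70.9% | 74.0% |
| 20% | 10.40 | 61.1% | 64.6% |

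**3. How much is due to the scoring rule.** If 10% of women were simply excluded, so that the size fell but the rates did not, power would be 75.6% with the correction and 78.5% without. The rule therefore costs about 4.7 and 4.5 points more than the loss of numbers alone. For the same reason the usual inflation, 320/(1 − 0.10) = 356 per arm, would not restore 80% by the protocol's own method; that would need 393.

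**The case against.** - **The 80% has some slack.** A reader might infer that any dropout at all takes power below 80%. The documents do not support that. The continuity correction is inferred from reproducing 320. Statistical method names a chi-square test, relative risks and GEE, and mentions no correction. On an uncorrected basis power starts at 82.6% and stays at or above 80% up to about 3% loss. This stands, and the point is limited accordingly.
- **The protocol does not forecast loss.** The dropout sentence is conditional and gives no rate. A reader might infer that the trial simply lacks its stated power; that goes too far, because the shortfall depends on a rate that the documents do not supply. This stands too.
- **Not every dropout has a missing delivery outcome.** Place of delivery is fixed at birth. Delivery status is to be tracked by fieldworkers and health professionals (Control arm B), and medical records are used to cross-check both primary and secondary outcomes (Secondary outcomes). A woman lost after a recorded delivery need not be scored as a non-user. So L must be read as the proportion with a missing delivery outcome, which may be smaller than the dropout proportion.
- **The 47% and 60% might already count losses as non-events.** The protocol does not say. If they do, multiplying by (1 − L) counts the dilution twice.
- **320 might be 299 plus a margin of about 7% for loss.** Nothing in the text says so; only clustering is named. It would not suffice in any case: under the scoring rule, uncorrected power has already fallen to 78.4% at 5% loss.
- **Such detail belongs in a fuller document.** The point is not that a detail is absent. The article asserts that 640 women suffice and also fixes a scoring rule that erodes that assertion.

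**Conclusion.** The point holds in limited form. The arithmetic behind 320 is correct, but it is the size for complete outcome data. Under the protocol's own scoring rule, 80% power is not kept beyond minimal loss of the delivery outcome: essentially none by the continuity-corrected method that reproduces 320, and about 3% without the correction. The power at higher losses illustrates the size of the shortfall and does not predict it.

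The figures rest on four assumptions: loss equal in both arms (unequal loss would also bias the comparison), loss unrelated to place of delivery, rates of 47% and 60% that do not already include losses as non-users, and the design effect of 1.3 taken at face value. The last is a separate and larger doubt, because the trial has one district and one health centre per arm. The figures here should not be read as endorsing it.

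**What to change.** Keep 640 women. In Assumption and hypothesis for sample size calculation, replace the statement that this number is sufficient with three items:

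1. the proportion of missing delivery outcomes that the investigators expect, after delivery tracking and record checks;
2. the power at that proportion, calculated with missing counted as non-use, and whether a continuity correction was used;
3. a sentence saying that this power is conditional on the design effect of 1.3 and on the 47% and 60% not already counting losses as non-users.

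The 5%, 10% and 20% used here are assumptions and should not be copied into the protocol as expected rates. The change restates a figure and needs no extra women. Its cost is a less favourable stated power.
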